$\beta_{t}$ is the fixed time effect, $X_{ijt}$ is the indicator of treatment mode for subject i cluster j at month t, θ represents the 3WP implementation effect, $Z_{ijt}$ are pre-specified patient and practice level covariates and $\in_{ijt}$ is random errors. We will also approximate the secular time trend $\beta_{t}$ linearly in time with βt. This model will accommodate unobserved center effects. All analyses will be carried out based on the intention to treat principle, which means that the treatment mode variable ($X_{ijt})$ is determined by the scheduled initiation of implementation based on randomization, but not by individual patient/family enrollment in the 3WP. Covariates, including age, sex, race/ethnicity, language, insurance status, and utilization of life-support measures, will be included in the model. We will also perform “as-treated” analyses to compare patients before implementation and patients who received 3WP after implementation and those who did not. Subgroup analyses will evaluate how outcomes are affected by race, ethnicity, and sex as a biological variable.

**Power calculations.** The primary outcome is the family-reported ESS factor score on the BFS, and the secondary endpoints include BFS-PM, FS-ICU, HADS and PCL-5. Across the 3 SNH ICUs, we estimate that 375 (90%) deaths per year will qualify for after-death surveys About 40% of families will return the survey based on our prior work [58,59]. With approximately 100 surveys returned before and 275 surveys after 3WP implementation and a 2-sided significance (α) level of 0.05, we will have 89.3% power to demonstrate the difference in the BFS ESS factor based on our preliminary data [59].

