### 3.7. Status and timeline

We have engaged stakeholders across the 3 SNH’s in individual or group interviews to refine and tailor the implementation plan (section 3.4). Thirty stakeholders participated: 4 unit directors, 11 charge nurses, 3 nurse educators, 7 physicians, 1 palliative care nurse, and 4 bedside ICU nurses). To obtain initial engagement and provide training (core function #1), stakeholders identified existing unit-specific meetings where 3WP can be promoted and formal training provided when appropriate, such as monthly staff meetings, daily shift change huddles, and multidisciplinary rounds. To facilitate bedside wish elicitation (#2), stakeholders recommended badge buddies and a script for nurses to reference, and informational brochures written in patient-preferred languages. To facilitate wish fulfillment (#2), sites recommended establishing an inventory of items to meet the cultural and spiritual needs of a majority Catholic patient population (rosaries, flameless prayer candles, Bibles). The electronic medical record was determined to be the ideal method for documenting 3WP participation (#3). Unit bulletin boards, health system-wide monthly newsletters, and computer screensavers were identified as spaces to recognize 3WP achievements and sustain unit engagement (#4).

3WP implementation occurred at the first SNH on April 1, 2024 and then staggered by 2 months for the subsequent two SNH’s. After-death surveys were first mailed to families of deceased patients on January 2, 2024 and will continue for 3.5 years (approximately ending in June 1, 2027). Survey data will be analyzed, and we anticipate that the results will be ready in 2028. The first family interview was conducted in August 2024. We anticipate that 30–36 interviews will be completed in two years and qualitative analysis of these interviews will be completed in 2027.

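### The 89.3% power rests on before/after survey counts and shows no allowance for the time adjustment and three-cluster stepping of the specified model

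*Protocol article*

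**What the plan says.** The power paragraph in Section 3.6.1 estimates "we estimate that 375 (90%) deaths per year will qualify for after-death surveys" and a 40% return rate. The survey counts it uses are given as "With approximately 100 surveys returned before and 275 surveys after 3WP implementation". Testing is two-sided at the 5% level. The conclusion drawn from these inputs is that "we will have 89.3% power to demonstrate the difference in the BFS ESS factor based on our preliminary data". The paragraph mentions no clusters, steps, intracluster correlation (ICC) or time adjustment.

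The statistical analysis paragraph in the same section specifies a mixed model with a random centre effect, a treatment indicator indexed by month, and a term that "is the fixed time effect". It adds a second version: "We will also approximate the secular time trend" by a straight line. It does not say which version is primary.

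On timing, Section 3.7 reports that "3WP implementation occurred at the first SNH on April 1, 2024 and then staggered by 2 months" for the other two hospitals. The Abstract gives 6–10 months of surveys before implementation at each site. Section 3.1 ends survey collection after 2.5 years, while Section 3.7 gives 3.5 years. The Discussion (Section 4) defends three clusters as an acceptable number without linking this to power.

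**The concern.** On its face the power sentence describes a comparison of 100 surveys with 275. The planned test is different: it estimates the 3WP effect after adjusting for centre and calendar time. With three ICUs switching within four months, treatment and time are almost aligned, so much of the before/after contrast is attributed to time once time is in the model. If the stated power ignores this, a null primary result could be read as coming from a trial with about 90% power when the specified test had much less.

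**Working it through.** **Inputs from the protocol article**
- 375 eligible deaths per year × 0.40 = 150 surveys per year; over 2.5 years, 375 surveys (Sections 3.6.1 and 3.1).
- Control periods of 6, 8 and 10 months (Abstract, with 2-month staggering) give 24 of 3 × 30 = 90 ICU-months. 24/90 × 375 = 100, which matches the stated split of 100 and 275.
- ICUs on and off 3WP coexist in months 7–10 only: 4 × 12.5 = 50 surveys. In 20 of the 30 months every ICU is on 3WP.

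**Assumptions (not in the document):** equal ICU sizes, so 375/90 = 4.17 surveys per ICU-month; ICC from 0 to 0.10, or fixed centre effects; total variance 1; known variance components; no covariates.

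**Step 1, the plan's own figure.** It cannot be reproduced forwards because no effect or SD is stated. It can only be inverted. For a two-group comparison, SE = √(1/100 + 1/275) = 0.1168 SD, and d = (1.960 + 1.243) × 0.1168 = 0.374 SD (0.375 with the t distribution).

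**Step 2, variance under the specified model.** The variance of the treatment effect θ is the θ entry of (X′V⁻¹X)⁻¹. X holds the treatment indicator and the time terms (plus centre terms if fixed). V has (1 − ICC)/4.17 per ICU-month mean, plus ICC shared within an ICU. Power = Φ(d/SE − 1.96). Ranges run over the ICC values and fixed centre effects.

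| Time term, 30 months | SE | Variance ÷ two-group variance | Power at d = 0.374 | Effect for 89.3% power |
|---|---|---|---|---|
| None | 0.112–0.118 | 0.91–1.02 | 89–92% | 0.36–0.38 |
| Linear trend | 0.172–0.181 | 2.2–2.4 | 54–59% | 0.55–0.58 |
| Month effects | 0.299–0.316 | 6.6–7.3 | 22–24% | 0.96–1.01 |

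Worked at ICC 0.01:
- Linear: 0.374/0.1789 − 1.96 = 0.13, so power is 55%. Effect needed: 3.203 × 0.1789 = 0.57.
- Month effects: 0.374/0.3072 − 1.96 = −0.74, so power is 23%. Effect needed: 3.203 × 0.3072 = 0.98.

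The variance ratios do not depend on d. The row with no time term shows that the loss comes from the time adjustment, not from the ICC.

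**Step 3, sensitivity at d ≈ 0.374**
- Coarser periods (random centre effect): 3-month 26–28%, 6-month 33–35%, 12-month 58–61%. Fixed centre effects give one to two points less.
- Surveys for 42 months (525 surveys): linear trend 70–74% (69% with fixed centre effects); month effects 22–25%.
- Unequal ICU sizes (several splits, fixed centre effects): linear 53–55%, month effects 17–23%.
- Control periods of 3, 5 and 7 months, counting from the first mailing to roll-out: linear 54–58%, month effects 22–24%.

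**The case against.** The strongest objection is that the inference about method is circular. With the effect unknown, some value of d gives 89.3% under any method, so the fact that a two-group test gives 89.3% at 0.374 SD says nothing about what was done. The article refers only to "to demonstrate the difference in the BFS ESS factor based on our preliminary data", and those data are not shown. A larger preliminary effect would look better: at ICC 0.01 and 30 months, 0.5 SD gives 80% (linear) and 37% (month effects), and 0.6 SD gives 92% and 50%. This stands. A reader might infer that 89.3% is certainly a t-test figure and that the trial has 23% or 55% power; the document does not support either statement.

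Two further points also stand. The linear-trend figure depends on which survey duration is used, and the 3.5 years in Section 3.7 raises it to about 70–74%. And a fixed time effect need not mean one term per month; longer periods give higher power, though still well below 89.3% at the implied effect.

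A journal article may also leave the effect size, SD and ICC to the full protocol, so their absence is not the defect. What remains is that one power figure sits beside two time specifications, and no single effect gives 89.3% under both.

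**Conclusion.** The point holds in conditional form. The power statement uses before/after counts and shows no allowance for the time adjustment and three-cluster stepping that the analysis specifies.

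One result does not depend on the unknown effect: over 30 months with equal ICUs, the variance of the treatment effect is about 2.2–2.4 times (linear trend) or 6.6–7.3 times (month effects) that of a 100-versus-275 comparison. Either the preliminary effect is near 0.57 SD and 89.3% applies to the linear version only, or it is near 0.98 SD and applies to month effects only, or the figure does not describe the specified analysis. In the last case, if it is a two-group figure, power is about 54–59% (linear, 30 months), 70–74% (linear, 42 months) or 22–24% (month effects).

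These powers rest on the back-solved effect, the assumed ICC range and ICU sizes, and a normal approximation without small-sample correction for three clusters.

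**What to change.** Recompute the power under the specified stepped-wedge model and restate it in Section 3.6.1. Name one time specification (month effects, longer periods or a linear trend) as primary and give the power for that one. Use the actual roll-out dates, expected surveys per ICU-month, the survey duration that will apply, an ICC range and the effect from the preliminary data. If 89.3% is kept, label it as the power of an unadjusted before-after comparison. Qualify the Discussion statement on three clusters with the restated figure.

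The cost is one recalculation and some wording, with no extra patients. The stated power will probably be less favourable. Section 3.7 plans survey collection to about June 2027 and results in 2028, so this can be done before the analysis.

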#### 3.6.2. Nurse outcomes.

Secondary outcomes include changes in nurse burnout as assessed by MBI-HSS, which consists of 22 items utilizing 7-point Likert scale responses ranging from 0 (never) to 6 (everyday) on items aimed at measuring the 3 dimensions of burnout [63]. The scores of the items in each MBI dimension will be summed; high scores for emotional exhaustion and depersonalization indicate higher levels of burnout, while high scores for personal accomplishment indicate lower levels of burnout. According to a recent meta-analysis on interventions that reduce clinician burnout [68], we anticipate that the 3WP will reduce the burnout by about 0.3–0.45 in effect size. With 150 nurse evaluations at each time point (60% response rate), we will have >85% power to detect a difference the MBI emotional exhaustion scale. This calculation conservatively assumes 0.5 correlations between before and after survey from the same nurses. We will use linear mixed effects to assess the effect of the 3WP intervention on nursing burnout, with nurses as a random effect, within the stepped-wedge study design. The analysis will control for nurse characteristics (i.e., age, sex, race, ethnicity, and years of experience) as well as the unique nurse identifier.

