#### 3.5.2. Surveys.

An after-death survey that assesses perceptions regarding EOL care (Bereaved Family Survey (BFS)) [55] and psychological symptoms (Hospital Anxiety and Depression Scale (HADS) [56] and PTSD Checklist for DSM-5 (PCL-5) [57]) will be mailed to each family of an ICU decedent throughout the study period, 3 months after the patient’s death (both pre- and post-intervention) (Fig 1). The postal mailing will include a stamped return envelope, a phone number and email address for questions, and a letter stating that completing the survey implies consent and that there will be a $40 honorarium for completion. Surveys will be tracked using a unique code. Two weeks following the initial mailing, non-responders will be called up to 3 times (at least one attempt after 5pm and maximum two voice messages) to remind families to mail it back, or to complete it by phone or online. We are anticipating a return rate of approximately 40% based on our group’s prior experience [58,59] and other studies evaluating the quality of dying [60–62].

All nurses in participating ICUs will be invited to complete on-line surveys during the month prior to 3WP training and at 6 and 12 months after 3WP implementation. The survey will include the Maslach Burnout Inventory-Human Services Survey (MBI-HSS) [63] as well as questions regarding nurse’s age, sex, race/ethnicity, marital status, years of experience, average number of hours worked per week, and whether the nurse works day or night shift. Surveys will also ask nurses to rank 4 statements (0–4 scale) to assess the extent of implementation fidelity to core functions: 1) The introductory/training sessions provided me with the necessary instructions for 3WP implementation. 2) Available tools and materials made it easy to implement 3WP at the bedside. 3) I feel comfortable documenting 3WP implementation. 4) My ICU has embraced the 3WP as a unit-level intervention. There are approximately 250 ICU nurses across the 3 SNHs and we are anticipating 150 nurse evaluations at each time point (60% response rate). The survey will take 10–15 minutes to complete, will be compensated with a $20 gift card, and will include coded identifiers to link pre- and post-implementation surveys.

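### The >85% power for nurse emotional exhaustion is a before/after figure; with the calendar-time adjustment of the article's stepped-wedge model, power is about 42–58% at effect 0.3 and 75–90% at 0.45

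*Protocol article*

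**What the plan says.** Section 3.6.2 of the protocol article gives the planned effect, "we anticipate that the 3WP will reduce the burnout by about 0.3–0.45 in effect size", and then the power claim, "With 150 nurse evaluations at each time point (60% response rate), we will have >85% power to detect a difference the MBI emotional exhaustion scale". The correlation input follows: "This calculation conservatively assumes 0.5 correlations between before and after survey from the same nurses". No time effect, ICU effect or stagger is mentioned in the calculation.

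The paragraph then names the analysis: linear mixed effects, "with nurses as a random effect, within the stepped-wedge study design", controlling for nurse characteristics.

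Section 3.5.2 schedules the nurse surveys "during the month prior to 3WP training and at 6 and 12 months after 3WP implementation" and gives the pool: "There are approximately 250 ICU nurses across the 3 SNHs and we are anticipating 150 nurse evaluations at each time point (60% response rate". Section 3.1 puts training one week before roll-out and staggers the three starts by 2 months.

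The only stepped-wedge model written out is in section 3.6.1, for family outcomes. It has a center effect and a fixed time effect, and the time trend is also to be approximated linearly.

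**The concern.** The power inputs are those of a before/after contrast: two surveys, a correlation between them and a standardised difference. A stepped-wedge analysis also has to separate the intervention from calendar time. Here that is hard. Starts are only 2 months apart, while the follow-up surveys come 6 and 12 months later, so before/after status is strongly correlated with the calendar. A calculation without time can therefore greatly overstate what a time-adjusted model delivers.

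The Introduction counts nurse burnout among the study's two key clinical outcomes, and >85% is its only power figure. If the time-adjusted model would miss an effect of 0.3 about half the time, a null nurse result could be given more weight against that effect than it can bear.

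**Working it through.** **Inputs.** From section 3.6.2: effect d = 0.3–0.45 (SD 1), 150 evaluations per wave, correlation ρ = 0.5. From section 3.5.2: one wave before and two after (6 and 12 months), from a pool of about 250. From section 3.1: three ICUs, starts at months 0, 2 and 4. The baseline survey falls in the month before training, and training is one week before the start, so baseline lies about 1.25 to 0.25 months before the start.

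Assumptions: about 50 evaluations per ICU per wave, and two-sided α = 0.05 (stated for the family outcome only). Throughout, power = Φ(d/SE − 1.96).

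**Step 1: the plan's figure, two waves and no time term.** With m nurses answering both waves, the difference in means has variance 2/150 − 2(0.5)m/150². At d = 0.3:

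| Nurses in both waves | SE | Power |
|---|---|---|
| 0 | 0.1155 | 73.8% |
| 50 (minimum overlap: 150 + 150 − 250) | 0.1054 | 81.2% |
| 90 (0.6 × 0.6 × 250) | 0.0966 | 87.4% |
| 150 | 0.0816 | 95.7% |

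Generalised least squares, which weights paired and unpaired nurses optimally, gives 85.1% with 50 and 90.8% with 90. So >85% at 0.3 is reproduced as a before/after figure under reasonable overlap.

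**Step 2: three waves, still no time term.** Take the same 150 nurses at every wave. The treatment indicator within a nurse is (0, 1, 1), with sum of squares about its mean Sxx = 4/9 + 1/9 + 1/9 = 2/3. The variance is (1 − ρ)/(150 × Sxx) = 0.5/100 = 0.005, so SE = 0.071 and power at 0.3 is 98.9%. With independent 60% response at each wave, SE = 0.077 and power is 97.3%.

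**Step 3: add a linear calendar trend.** With ICU effects and the same 150 nurses, Var = (1 − ρ)/[150 × Sxx × (1 − r²)], where r is the within-nurse correlation of treatment and time. For baseline at month −1:

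- Times are (−1, 6, 12), mean 5.667, sum of squares Stt = 84.667, cross-product Sxt = 6.667.
- r² = 6.667²/(0.6667 × 84.667) = 0.787.
- Var = 0.5/[100 × (1 − 0.787)] = 0.0235, so SE = 0.153, against 0.071 without time.
- Power at 0.3: Φ(0.3/0.1534 − 1.96) = 49.9%. At 0.375 it is 68.6% and at 0.45 it is 83.5%.

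In this case the 2-month stagger drops out: moving an ICU's three dates together is absorbed by its ICU effect. The trend is then learned only from the step between 6 and 12 months.

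**Step 4: vary what the article leaves open.** Power at 0.3 / 0.375 / 0.45 by generalised least squares:

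| Baseline (months) | ICU effects | Same 150 nurses at all waves | Independent 60% response |
|---|---|---|---|
| −1.25 | yes | 48 / 67 / 82% | 42 / 59 / 75% |
| −1.25 | no | 52 / 71 / 85% | 47 / 65 / 80% |
| −1 | yes | 50 / 69 / 84% | 43 / 61 / 77% |
| −1 | no | 53 / 72 / 86% | 48 / 67 / 82% |
| −0.25 | yes | 55 / 74 / 88% | 48 / 66 / 82% |
| −0.25 | no | 58 / 77 / 90% | 53 / 72 / 86% |

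Standard errors run from 0.139 to 0.171. No case reaches 85% at 0.3 or 0.375; several do at 0.45. With baseline at month −1, the same 150 nurses and ICU effects, ρ would have to be about 0.79 for 85% at 0.3. Splitting the 150 nurses unequally across ICUs (30, 50 and 70, for example) leaves the 49.9% unchanged.

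**The case against.** **The nurse model is not written out.** This stands as a caveat. The equation in section 3.6.1 is given for family outcomes, and section 3.6.2 prints neither a time term nor an ICU term for nurses. A reader might infer that the article states a time-adjusted nurse model; it does not. But the stepped-wedge phrase has only one written meaning in this article, and that includes time. If no time term is intended, the nurse analysis is an uncontrolled before/after comparison and should be called one. Either reading calls for a correction.

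**The figure is not tied to 0.3.** This is also true. A reader might infer that power falls short across the whole planned range, or reaches 85% at 0.45 only in one best case. The table does not support that: five of the twelve cases exceed 85% at 0.45. The shortfall lies at the lower end and middle of the range, to which >85% is attached without restriction.

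**The arithmetic is not wrong.** Agreed. The printed figure follows from its inputs, although the exact calculation used has to be inferred. The problem is the mismatch between the power method and the analysis.

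**The word conservatively is legitimate.** It qualifies the 0.5 correlation only, and a higher correlation would raise power. Nothing in the article shows 0.5 to be optimistic, so the word may stay. It should not be read as describing the power figure as a whole.

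**A reader might infer that the effect cannot be estimated at all.** With a separate effect for each month that would follow: with baseline at month −1 the nine ICU-waves fall in nine different months (−1, 1, 3, 6, 8, 10, 12, 14, 16). But the article also offers a linear trend in its family model, under which the effect is estimable, so this point does not rest on that reading.

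**The outcome is secondary and no sample size depends on it.** Correct: all nurses are invited. That limits the weight of the point but does not make the printed figure fit the analysis.

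**Conclusion.** The point holds as a mismatch between a printed power figure and the analysis named in the same paragraph. It should be corrected, but it does not threaten the conduct of the trial. At 0.3, >85% is a before/after figure without calendar time. With a linear trend the standard error about doubles (0.071–0.077 to 0.139–0.171), and power is about 42–58% at 0.3, 59–77% at 0.375 and 75–90% at 0.45. At the lower planned effect the gap to 85% is at least 27 points (85 − 58).

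This rests on reading the stepped-wedge phrase as including a time term, and on about 50 evaluations per ICU per wave, two-sided 0.05, ρ = 0.5 and baseline 1.25 to 0.25 months before the start. The linear trend is the favourable form of time adjustment.

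**What to change.** Choose one of two changes in section 3.6.2:

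1. Restate nurse power for the time-adjusted stepped-wedge model at both 0.3 and 0.45, with the form of the time term, baseline timing, response overlap and any ICU effect stated. On the inputs above this is roughly 40–60% at 0.3 and 75–90% at 0.45; the study team should compute the final figures from its actual survey dates and ICU sizes.
2. If no time term is intended, label >85% as the power of an uncontrolled before/after comparison, and describe the nurse result in those terms.

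If the word conservatively stays, it should remain attached to the correlation assumption alone. The cost is one or two sentences, with no extra nurses or data. Under the first option the stated power becomes less favourable; under the second, the nurse result can no longer be presented as a stepped-wedge comparison.

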**Methods:**

We conduct a pragmatic cluster-randomized stepped wedge type 2 hybrid effectiveness-implementation study to implement and evaluate the effect of the 3WP (compared to usual care) on quality of EOL ICU care, bereaved families’ psychological symptoms, and clinician burnout. Prior to implementation, interviews with stakeholders from each hospital will refine the implementation strategy. Starting 6–10 months prior to 3WP implementation at each site and continuing throughout the study, we will survey bereaved families once 3 months after each patient’s death. Surveys will query: EOL care, anxiety, depression, and post-traumatic stress disorder (PTSD). Each SNH ICU starts the 3WP at a randomly assigned time that is staggered by 2 months. Nurses are surveyed on burnout before implementation, 6 months, and 12 months after 3WP implementation. Semi-structured interviews are conducted with 10–12 family members per SNH who received 3WP and 10–12 nurses per SNH a year after implementation. We will use the RE-AIM (Reach, Effectiveness, Adoption, Implementation, and Maintenance) framework to guide a mixed-methods evaluation of the 3WP implementation in SNHs.

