## 3. Methods

### 3.1. Overview

Prior to implementing the 3WP intervention, we will refine the components of the implementation strategy (below) by engaging stakeholders at each SNH. We will then use a cluster-randomized stepped-wedge type 2 hybrid effectiveness-implementation design to implement the 3WP and assess its effectiveness in improving the EOL experience for SNH patients and their families. One week prior to intervention roll-out, we will conduct training sessions with ICU nurses that go over 3WP objectives, ways to introduce the 3WP to patients and families, and resources available. We will establish a tailored inventory of items that can be used in wish fulfillment based on prior experience and suggestions from each SNH. A research assistant at each SNH will assist with logistics, support nurses with wish implementation if needed, and collect data. Each SNH ICU (cluster) begins in the control phase and will start 3WP implementation at a randomly assigned time (wedge) (Fig 1). Implementation at each center will be staggered by 2 months. This design is useful in situations where 1) there is evidence of efficacy [23,24,26–30] and there is more potential for the intervention to do good than harm, 2) the traditional experimental randomization may be viewed as inappropriate given the nature of the intervention (a stepped-wedge design would allow all safety-net ICUs to initiate the 3WP), and 3) there are logistical constraints to randomization (3WP is a unit-level intervention and randomization at the patient level will likely result in contamination) [44,45].

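### The nurse surveys give no calendar month or quarter with both control and 3WP responses, so the burnout analysis is a before-after comparison and not a stepped-wedge one

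*Protocol article*

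**What the plan says.** All references are to the protocol article.

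- **Analysis.** Section 3.6.2 (Nurse outcomes) plans a linear mixed model for the 3WP effect "on nursing burnout, with nurses as a random effect, within the stepped-wedge study design". It lists nurse covariates and gives no time term.
- **Survey times.** Section 3.5.2 invites all ICU nurses "during the month prior to 3WP training and at 6 and 12 months after 3WP implementation". The abstract agrees: "Nurses are surveyed on burnout before implementation, 6 months, and 12 months after 3WP implementation".
- **Roll-out.** Section 3.1: "Implementation at each center will be staggered by 2 months". Section 3.7: "3WP implementation occurred at the first SNH on April 1, 2024 and then staggered by 2 months" for the other two hospitals.
- **Training.** Section 3.1: "One week prior to intervention roll-out, we will conduct training sessions with ICU nurses".
- **Time in the stepped-wedge model.** Section 3.6.1 writes the model for patient and family outcomes. Its month-indexed term "is the fixed time effect", and a linear version is added ("We will also approximate the secular time trend" linearly).
- **Power.** Section 3.6.2 claims more than 85% for emotional exhaustion, from 150 evaluations per time point, an effect size of 0.3–0.45 and a before-after correlation of 0.5 within nurses.

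**The concern.** A stepped-wedge analysis separates an intervention from calendar time by comparing, within the same period, clusters that have crossed over with clusters that have not. The nurse surveys are tied to each ICU's own start, and the first post-start survey comes later than the whole roll-out takes. If no period holds both kinds of survey, the nurse data lack the feature that the stepped-wedge label promises.

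At stake is the reading of the burnout result. Burnout is formally secondary, but the Introduction names it as one of two key clinical outcomes, to be compared with usual care. The three ICUs belong to one county system, so a change in staffing, season or working conditions could reach all of them between the pre and post surveys. In an analysis without a time term, such a change would be read as an effect of 3WP. The limitations in the Discussion do not mention this.

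**Working it through.** **1. The plan's own power figure.** Inputs from Section 3.6.2: 150 evaluations per time point, correlation 0.5, effect size 0.3–0.45. Two-sided α = 0.05 is stated for the family outcome and assumed here for nurses. Let L be the number of nurses linked across the two surveys; the document does not give it.

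SE = √[(2/150) × (1 − 0.5 × L/150)]; power = Φ(effect/SE − 1.96).

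| Linked nurses L | SE | Power at 0.3 | Power at 0.45 |
|---|---|---|---|
| 150 (all) | 0.082 | 95.7% | above 99% |
| 90 (assumed 60% overlap) | 0.097 | 87.4% | above 99% |
| 0 | 0.115 | 73.8% | 97.4% |

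The claim of more than 85% therefore reproduces as a before-after contrast with no time term. At 0.3 it needs about half the respondents linked: L = 75 gives SE = √(0.01333 × 0.75) = 0.100 and power of 85.1%.

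**2. The calendar.** The starts for ICUs 2 and 3 are derived from the 2-month stagger.

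| ICU | Start | Control survey | 6-month survey | 12-month survey |
|---|---|---|---|---|
| 1 | 1 Apr 2024 | about Mar 2024 | Oct 2024 | Apr 2025 |
| 2 | about 1 Jun 2024 | about May 2024 | Dec 2024 | Jun 2025 |
| 3 | about 1 Aug 2024 | about Jul 2024 | Feb 2025 | Aug 2025 |

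Training is a week before roll-out, so the last control window closes about 25 July 2024. The first 3WP survey is due about 1 October. The gap is 2 to 3 months. It does not depend on the exact dates: counted from the first start, the last control survey comes before month 4 and the first 3WP survey at month 6.

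**3. Categorical time.** The 3WP indicator equals the sum of the period indicators from October 2024 onward, so it adds nothing to a model that already contains them. Rank of the design matrix for the nine ICU-by-survey cells, with ICU effects:

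- monthly: 9 without the indicator, 9 with it;
- quarterly: 8 without, 8 with.

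Dropping the ICU fixed effects changes nothing (9 and 9; 7 and 7), so random centre effects do not help.

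**4. Linear time.** With ICU effects and one common slope, the slope comes from the change between 6 and 12 months and is carried back to baseline. With the control survey 1 month before the start:

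estimate = (y₆ − y₀) − (7/6)(y₁₂ − y₆) = −y₀ + 2.17y₆ − 1.17y₁₂, where each y is an average over the three ICUs.

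Per unit cell variance, this has variance (1 + 2.17² + 1.17²)/3 = 2.35. The contrast without time has (1 + ½)/3 = 0.50. The ratio is 4.7.

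A nurse-level generalised least squares version (50 nurses per ICU per survey, same nurses followed, correlation 0.5, control survey 0.75 months before the start, centre variance from 0 to 10) gives:

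| Time term | SE (SD units) | Power at 0.3 | Power at 0.45 |
|---|---|---|---|
| None | 0.071 | 99% | about 100% |
| Linear | 0.144–0.150 | 51–55% | 85–88% |
| Categorical | not estimable | – | – |

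The variance ratio here is 0.0208/0.0050 = 4.2 to 0.0226/0.0050 = 4.5. At the ratio of 4.7, SE = √0.0235 = 0.153 and power is slightly lower: about 50% at 0.3 and 84% at 0.45.

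**The case against.** The calendar arithmetic is hard to dispute. The fair objections concern how far it reaches.

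- **The time term is written for families.** Section 3.6.1 gives the fixed time effect and the linear trend for patient and family outcomes. Section 3.6.2 gives none for nurses, and an unseen analysis plan may supply one. This stands: the rank result applies only if categorical time is carried over. But no choice of model can create concurrent control surveys.
- **A reader might infer that burnout cannot be analysed, or that 3WP is fully confounded with time.** That is exact only for categorical time in periods up to about a quarter. A linear trend makes the effect estimable. So do half-year periods (rank rises from 6 to 7), at variance 3.0 against 0.5, but only by treating July and October as one period.
- **A reader might infer that any system-wide trend will be reported as a 3WP effect.** That holds if time is left out. A linear term removes a linear trend and leaves non-linear change.
- **A reader might infer from the linear-trend weights that a growing benefit would get the wrong sign.** That depends on the scenario. If the benefit doubles from 6 to 12 months, the estimate is 2.17 − 1.17 × 2 = −0.17 of the 6-month effect. If it grows by half, it is 2.17 − 1.17 × 1.5 = +0.42, too small but with the right sign.
- **The article is partly open about this.** It speaks of changes in burnout, bases power on before and after surveys from the same nurses, and concedes that clinicians are not randomised. It does not say that secular trend is inseparable for nurses, and it still names the stepped-wedge design as the analysis frame.

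**Conclusion.** The point holds in a limited form. The nurse schedule contains no month or quarter in which control and 3WP surveys coexist, so Section 3.6.2 attributes to the burnout analysis a property that the data do not have. What can be estimated depends on the time term:

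- categorical, monthly to quarterly: nothing;
- linear: an effect resting on extrapolation, with roughly four to five times the variance and about even odds of detecting 0.3;
- none: an uncontrolled before-after change, the only version that matches the stated power.

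This rests on the 2-month stagger and the survey times being kept as described. The power figures further assume two-sided α = 0.05, the illustrative linkage values, and equal ICU sizes in the linear-trend check.

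The documents do not support the stronger reading that the nurse component is unanalysable or that its result must be spurious. They also give no ground for extending the point to the primary outcome, because families are surveyed continuously. The matter is a wrong description that limits what a secondary outcome can show; it is not a threat to the trial's main conclusion.

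**What to change.** In Section 3.6.2:

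1. Replace the stepped-wedge phrase with a before-after comparison at 6 and at 12 months: nurse random intercept, ICU fixed effect, survey wave as a factor.
2. State that the power of more than 85% refers to that linked before-after contrast, and give the number of linked nurses assumed.
3. State there and in the limitations that the result cannot be separated from secular trend.
4. If a linear-trend model is reported, make it a sensitivity analysis and state its lower power (about 51–55% at 0.3).

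The cost is wording and a weaker causal claim for a secondary outcome. No new data are needed. On the Section 3.7 dates the pre-roll-out survey windows have passed, so concurrent control surveys can no longer be added.
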